## 4. Potential Therapeutic Role in Oncology

Therapeutics based on NPs have been widely explored, resulting in many applications in clinical practice today. In the oncology therapeutic field, most studies focus on the use of NPs rather than on the potential role of the protein corona.

Recently, many studies have focused on the potential therapeutic role of NPs, particularly as drug delivery vectors. Research indicates that there are general requirements for an effective system for cancer treatments: NPs must be biocompatible, highly bioavailable, and stable under physiological conditions. They should be able to target only tumor cells without interfering with surrounding healthy cells and to release their load as soon as they reach the target site [15].

NPs’ size is the most influential factor for adequate biodistribution and effective drug delivery. Thanks to their relatively small size, NPs are very efficient at crossing membrane pores. Tumors have leaky vasculature, letting NPs easily penetrate small tumor vessels, while normal blood vessels typically prevent NP extravasation, thus avoiding agglomeration in other parts of the body. In general, smaller-sized particles (<50 nm) have better antitumoral efficiency. However, as different organs have different size uptake characteristics, research is focusing on this concept for the development of a more organ-specific cancer treatment [15,16].

In addition to size, NPs’ shape is a critical factor influencing interactions between molecules, controlling fluid dynamics and affecting cellular uptake. The reticuloendothelial system (RES) is the main site of nanomedicine storage, impacting the toxicity and immunogenicity of injected drugs [16]. The nano-drug delivery system undergoes three key steps in order to effectively reach the tumor. First, the nanoparticles circulate throughout the body, where they are partially engulfed by macrophages in the reticuloendothelial system. Next, they penetrate the tumor site and release the drugs. Finally, they accumulate in the tumor and exert therapeutic effects. However, before reaching the tumor, nanoparticles face several challenges, such as recognition as foreign bodies and phagocytosis by macrophages. These challenges can complicate the use of nanoparticles for tumor treatment, with only a low rate of nanoparticles ultimately reaching the tumor site. The protein coronas’ composition and interaction with NPs can help them escape the RES and macrophages’ interaction, ultimately improving drug delivery and transportation [16].

The complexity of the NP surface leads to varied interactions, degradation, agglomeration rates, and cellular uptake. Consequently, the protein corona–NP complex plays a major role in the biodistribution–biocirculation–biocompatibility of potential carried drugs. Recent research demonstrated that different surface properties may be necessary depending on cancer type and stage. To date, many strategies have been developed to assist tumor uptake of NPs. These strategies include manipulating NPs’ design (influencing tumor infiltration and/or retention of drugs), modifying the tumor microenvironment by the coadjutant retention of drugs, and modifying the tumor microenvironment by coadjutant treatments such as photodynamic therapy, radiotherapy, and immunotherapy [4].

Applications in clinical practice may be the utilization of gold NPs because of their optical and tunable properties, with an easy modifiability due to their negative surface charge. For instance, Methotrexate (MTX) conjugated with gold NPs has higher cytotoxicity than MTX alone. Doxorubicin (DOX) has higher potential against the multidrug resistant MCF-7/ADR breast cancer cell line if conjugated with gold NPs. Other examples may include the conjugation of gold NPs with peptide–drug conjugates (PDCs) and phytochemicals such as kaempferol [17,18]. In 2007, Chen YHP et al. [18] proposed a new MTX formulation (MTX-AuNP conjugate) to prolong drug retention in tumor cells and alter its pharmacokinetic behavior. Spectroscopic examinations were conducted revealing how MTX accumulation is faster and higher in tumor cells treated with MTX-AuNP than those treated with free MTX. Moreover, MTX-AuNP showed higher cytotoxic efficacy on several tumor cell lines when compared with an equal dose of free MTX. In a recent study on mouse models of ascites Lewis lung carcinoma (LL2), the administration of MTX-AuNP rather than an equal dose of free MTX significantly (*p* = 0.0041) increased tumor growth suppression [15].

NPs have the ability to overcome solubility and stability problems of anticancer drugs by encapsulating the compound within a hydrophilic nanocarrier. When perishable, drugs can also be paired with synthetic nanocarriers. NPs’ physicochemical properties enhance drug penetration and redirection, allowing passive or active targeting in a selective manner. Additionally, nanocarriers can influence the circulation time of a drug by expelling upon contact with specific environmental factors (such as pH), resulting in a stimuli-sensitive treatment [17].

An example of targeting is represented by the optimization of anti-HER2 monoclonal antibodies, creating “nanobodies”: they consist of the antigen-binding domain of the heavy chain-only camelid antibody, showing greater stability, assembled through covalent binding [17]. In 2017, D’Hollander et al. proposed a chemical strategy to overcome protein corona-targeting issues in in vivo biological systems by reducing their thickness. Nanobodies were covalently bound to AuNPs through a self-assembled monolayer interface. They found an optimal blocking agent (2-mercapto ethanol), interfering with the active groups of the self-assembled monolayer on AuNPs. Two cell lines were used to test this approach both in vitro and in vivo in a mouse model: an ovarian cancer cell line (SKOV3) showing high HER2-receptor expression and a hamster ovarian cancer cell line (CHO) as a negative control. Through darkfield microscopy and photoacoustic imaging, it was seen how a reduction in the protein corona size increased the specificity of the functionalized molecules towards HER2-expressing tumor cells [17].

Immunotherapy may benefit from these findings, as the protein corona coating on NPs’ surface could modulate immune response. On the one hand, precoated molecules, such as liposomes, may reduce immunogenicity. On the other hand, protein coronas can act as ligands of immune receptors, causing a cytokine storm and stimulating macrophages to produce a pro-inflammatory response [18]. Cai R. et al. discovered that interleukin-1β (IL-1β) levels are positively correlated with the abundance of immune-related proteins within the protein corona coating [19]. Since the surface chemistry-induced specific protein corona affects the phagocytosis and immune responses of macrophages, it can influence the internalization pathways and cytokine secretion profiles of macrophages. The release of interleukin-1β (IL-1β) by macrophages is directly dependent on the number of proteins involved in immune responses (e.g., acute phase, complement, and tissue leakage proteins) present in the acquired nanoparticle corona [20].

### Key Points Summary

Few studies have focused on the potential therapeutic role of NPs, especially on their possible use as vectors for drug delivery. NPs designed for this purpose must be biocompatible, highly bioavailable, and stable under physiological conditions. They should be able to target only tumor cells without interfering with surrounding healthy cells and to release their load as soon as they reach the target site. NPs’ size is the most influential factor in biodistribution and delivery. Their role in optimizing monoclonal antibody, immunotherapy, and chemotherapy targeting has also been investigated.

## 5. Advances in Prostate Cancer

Currently, there are few studies in the existing literature specifically focused on the applications of NPs in prostate cancer (PCa) treatment, either as diagnostic or therapeutic tools.

### 5.1. Diagnostic Applications

Recently, the concepts of protein coronas, sensor arrays, and supervised classifiers were merged to create the concept of a “protein corona sensor array”, aimed at effectively identifying and distinguishing diseases.

Digiacomo L. et al. [20], in 2020, established the experimental validation capabilities of the protein corona sensor network in oncology and neurodegenerative disorders. This research assesses the viability of identifying breast and prostate cancers using the protein corona sensor array platform. To achieve this goal, they utilized three cross-reactive liposomal formulations with unique physicochemical characteristics, leading to varying affinities for specific plasma proteins. This strategy can significantly enhance the quantity and diversity of plasma proteins potentially linked to cancer. By utilizing arrays of NPs with unique physiochemical traits, distinct protein corona profiles can be produced. This indicates that a single NP type’s protein corona composition could yield unique ‘fingerprints’ for each condition. In this investigation, three liposomal formulations with differing lipid compositions and surface charges were exposed to human plasma from patients diagnosed with two prevalent cancer types, breast cancer and PCa, alongside a control group of healthy donors. Instead of targeting a specific biomarker, they examined alterations in the protein profiles that facilitate the differentiation between patients with and without cancer. Overall, the size, zeta potential, and nano-liquid chromatography–tandem mass spectrometry findings suggest that the liposome corona is influenced by the liposomes’ surface chemistry and varies across different cancer types. Utilizing statistical methods, they were ranked based on their capability to distinguish between individuals with and without cancer. Significantly, the proteins demonstrating the highest discrimination potential were clearly linked to various cancer aspects. One important process in tumor development is angiogenesis, the physiological mechanism through which new blood and lymph vessels arise from pre-existing vessels, supplying tumors with necessary nutrients and cytokines for the growth and systemic spread of cancer cells. The coronas of cancer patients revealed several proteins associated with angiogenesis. The coronas from cancer patients showed substantial differences from those of healthy individuals in its levels of FBLN1, which belongs to the fibulin family, a class of proteins involved in organizing the stromal matrix. The results showed a clear separation of cancer patients and control subjects in two-dimensional spaces with axes defined by corona proteins with the highest discrimination ability. Following incubation with HP from healthy individuals, 178, 256, and 179 proteins were identified in the coronas of L1−HP, L2–HP, and L3–HP complexes, respectively. The percentage of proteins common to all three formulations spanned from ≈50% (L2–HP complexes) to ≈72% (L1–HP and L3–HP complexes). However, unique proteins comprised a minor fraction of the coronas, with the coverage percentage ranging from ≈7% (L1–HP complexes) to ≈29% (L2–HP complexes). After their interaction with HP from breast cancer and prostate cancer patients, similar results were obtained. Coronas from cancer patients and healthy individuals were compared and RPA values of breast cancer and control groups were statistically different in 172 proteins (L1: *n* = 62; L2: *n* = 71; and L3: *n* = 39). This number was 157 when the coronas of PCa patients and control subjects were compared (L1: *n* = 55; L2: *n* = 58; and L3: *n* = 44). This characterization has potential for improving the early detection of cancer using a simple blood test [19].

Huo Qu et al. [21] in 2011 developed an NP immunoassay for serum protein biomarker detection and analysis in which a serum sample was first mixed with a citrate-protected AuNP solution. Proteins from the serum were adsorbed to the AuNPs to form a protein corona on the NPs’ surface. An antibody solution was then added to the assay solution to analyze the target proteins of interest that were present in the protein corona. The protein corona formation and the subsequent binding of antibodies to the target proteins in the protein corona were detected by dynamic light scattering (DLS). They discovered multiple molecular aberrations associated with PCA from mouse and human blood serum samples. From the mouse serum study, they observed differences in the size of the protein corona and mouse IgG level between different mouse groups. The experiment enclosed the mouse implantation of the rapidly proliferating prostate cancer cell line PC3, the slowly progressing tumor cell line LnCaP, and a third group of mice treated with phosphate-buffered saline (PBS) solution as a control. Mice implanted with PC3 cells developed significantly larger tumors (measured in grams) than those injected with LnCaP cells (weighing in tens to hundreds of milligrams). The average weight ratio of the tumor over body weight was approximately 5% for the PC3 mice and less than 0.3% for the LnCaP mice. The average particle size increase in the healthy control group was 75 nm, significantly higher than the PC3 mice with an average particle size increase of 24 nm and an average particle size increase for LnCaP mice of 43 nm. It was also noticed that within the healthy control and the LnCaP mouse group, there were substantial variations between individual mice: the particle size increase varied from 20 to 110 nm for the LnCaP mice and from 40 to 120 nm for the healthy control mice with no prostate tumors in the control mice. Three groups of human serum samples were included in this study: normal healthy donors (*n* = 15); patients diagnosed with BPH (*n* = 10); and patients diagnosed with PCa with stages from T1c to T3b (*n* = 25). It was found from both the mouse model and the human serum sample study that the level of vascular endothelial growth factor (VEGF) adsorbed to the AuNPs was inferior in cancer samples compared to non-cancerous or less malignant cancer samples. This research demonstrates a notable disparity in the “size” of the serum protein corona that is formed on the surface of AuNPs between cancerous and non-cancerous or less aggressive tumor-bearing mouse models [21].

Ahmadianpour et al. [22], in 2020, studied the application of AuNPs for the early detection of PCa. In this study, blood samples of 60 male subjects aged 40–90 years were collected from 20 healthy individuals, 20 patients with BPH, and 20 patients with PCa. Optical scattering changes were measured by the level of AuNPs mixed with different sera, and the responses were compared with the PSA (Prostate-Specific Antigen) index of the subjects. No significant differences were found in the size of the corona protein structure between the three groups of males with PCa or BPH and healthy males. No correlation was found between the DLS concentration and PSA serum level due to changes in ambient temperature, prolonged test duration, or high IgG levels in apparently healthy individuals. They ascertained that DLS has major limitations for PCa detection, so it cannot be a simple and accurate method for the early detection of this tumor [22].

Lately, researchers have focused on tumor-linked exosomes through liquid biopsy evaluation, obtaining PSA exosomes with more sensitivity and specificity than traditional PSA blood analysis and representing a promising biomarker [3].

Logozzi et al. demonstrated how analyzing PSA-expressing exosomes can differentiate between healthy patients and those with prostate disease, also discerning into benign and malignant pathology. The study enrolled 240 male patients, of which 80 were controls, 80 had BPH, and 80 had PCa. Exosomes were extracted from an EDTA-treated blood sample using centrifugation; then, they were qualified and quantified using different methods. In particular, the IC-ELISA method had a 98.57% sensitivity and an 80.28% specificity in discriminating malignant from benign prostatic pathology. Also, combining IC-ELISA and NFSC led to an increase of up to 96% in sensitivity and 100% in specificity. Moreover, a significant (*p* < 0.0001) increase in the number of exosomes and a lower size in prostate cancer patients was demonstrated [3].

### 5.2. Therapeutic Applications

An ongoing clinical trial, active from 2020, is AuroLase^®^ NCT04240639, which provides ultra-focused tissue ablation therapy for solid tumors and aims to enhance treatment effectiveness while reducing the side effects commonly linked to surgery, radiation, and conventional focal therapies [23,24]. It employs the “optical tunability” of a novel class of NPs known as AuroShells, which absorb near-infrared wavelengths of light that harmlessly infiltrate human tissue and expose the tumor to a near-infrared laser. The NPs selectively seize the photonic laser energy, transforming the light into heat, effectively obliterating the tumor and its nourishing blood vessels while preserving adjacent tissues. AuroLase Therapy utilizes an FDA-approved laser that produces near-infrared energy within clinically defined parameters (output, duty cycle, duration) and incorporates an FDA-sanctioned fiber optic probe for percutaneous energy delivery. AuroShell particles (also referred to as “nanoshells”) feature a gold metal shell surrounding a non-conductive silica core, functioning as the external absorber of the near-infrared laser energy channeled by the probe. These AuroShells are introduced intravenously and, due to their diminutive size, they can gather in the tumor through its porous vasculature. NPs cannot penetrate normal blood vessels; hence, they do not accumulate in healthy tissues. Once concentrated in the tumor, the region is targeted with a near-infrared laser at carefully selected wavelengths to ensure maximum light penetration through tissues. The AuroShells are engineered to absorb this specific wavelength and convert the photonic laser energy into sufficient heat to ablate the tumor [24]. Nanospectra’s proprietary nanoshells navigate freely in the bloodstream and converge in the tumor. Utilizing cutting-edge imaging technology, the clinician precisely locates the prostatic lesion and positions the optical fiber probe through targeted MRI–ultrasound fusion technology on the prostate gland. PCa tissue could be ablated while preserving adjacent healthy tissue. Currently, AuroShell particles are investigational and can only be accessed through designated, FDA-authorized clinical study sites [24].

### 5.3. Key Points Summary

In the field of prostate cancer, research is in its initial phase. In the context of diagnostics, the use of PSA-expressing exosomes showed potentiality in better discrimination between PCa and BPH diseases. In the context of therapies, support for ultra-focused treatments and targeting appears to have the greatest application possibilities.

## 6. Experimental Trial: Protocol Design

### 6.1. Premise

Despite advances in genomics, proteomics, metabolomics, and lipidomics, to date there is still an absence of predictive protein and metabolic biomarkers. Proteomics and metabolomics approaches, based on mass spectrometry techniques, are undoubtedly of high interest but face challenges such as low sensitivity and specificity due to the low concentration levels of biomarkers in human plasma. Clinical application is further hampered by factors such as sample size, intra-individual variability, the presence of bias, and overall cost. These challenges highlight the complexity of using proteomic and metabolomic approaches for effective detection and treatment of PCa. The National Cancer Institute (NCI) recognizes the potential of technologies based on the use of nanoparticles in revolutionizing clinical approaches in the diagnosis and prognosis of cancer. Recent research suggests that once nanoparticles (NPs) come into contact with the biological fluid of cancer patients, they are covered by proteins, forming a “protein corona” composed of hundreds of plasma proteins. Hajipour and colleagues [25] introduced the concept of a personalized, disease-specific protein corona, demonstrating substantial differences in NP corona profiles between patients with and without cancer. As the protein corona field grew, limited interest in the metabolite corona began to emerge with investigations into the lipid composition of the corona around inhaled nanomaterials and, eventually, more holistic analyses of the metabolite corona. Chetwynd and co-workers [26] suggested that the metabolite corona coexists with the protein one since these smaller molecules can fit between proteins and are often bound into protein complexes. The metabolite corona is complementary to protein coronas, following similar rules of adsorption based on abundance and affinity, leading to metabolite fingerprints akin to protein fingerprints. Understanding how NPs interact with the metabolites in the biological milieu, particularly in cancer patients, holds promise for advancing diagnostic capabilities. The metabolite corona can provide valuable information about the individual’s metabolic profile, offering insights into the unique metabolic characteristics associated with cancer. In conjunction with the protein corona and other emerging concepts, it contributes to a more comprehensive understanding of the complex interactions between NPs and biological components. These insights may pave the way for innovative diagnostic approaches and personalized medicine strategies in cancer diagnosis and treatment.

### 6.2. Study Design

We developed the design of an experimental prospective single-center study with patients allocated in a 1:1:1 ratio of one of the three arms. A longitudinal analysis will also be applied to a 12-month interval observation. The protocol has been approved by our Ethic Committee Sapienza Policlinico Umberto I, Prot 0919/2021. The protocol will start on January 2025.

### 6.3. Endpoints

#### 6.3.1. Overall Aim

The protocol will aim to develop and implement sensitive nanotools with two distinct objectives. It will carry this out by designing nanoparticles (NPs) capable of selectively binding and detecting biomarkers in order to build a predictive diagnostic model to effectively discriminate between patient sera affected by benign prostatic hyperplasia (BPH) and prostate cancer (PCa). This initiative will be driven by improving diagnostic precision and accuracy, enabling early and accurate differentiation between these two conditions. Secondly, within the population with PCa, in cases of initial advanced metastatic diagnosis (mHSPC = metastatic hormone-sensitive prostate cancer), the objective will be to find biomarkers capable of predicting the response to systemic treatments to improve the precision and efficiency of monitoring treatment outcomes, leveraging the aforementioned nanotechnology and leading to the development of personalized therapeutic strategies for patients.

#### 6.3.2. Primary Endpoints

The first primary endpoint is the construction of predictive diagnostic models on serum from patients with a histological diagnosis of PCa versus patients with BPH using proteomics, metabolomics, and lipidomics of the biomolecular coronas that form between nanoparticles and serum.

A second endpoint is the construction of a predictive model for the response to treatment of patients with an initial diagnosis of mHSPC for the personalization of therapies and for the stratification of such patients considering individual characteristics such as genetics, lifestyle, and more, as foreseen by precision medicine, using metabolomics and lipidomics of the biomolecular coronas that form between nanoparticles and serum.

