### 6.4. Population and Eligibility Criteria

Three different populations will be considered and compared.
-Subgroup 1: Patients with initial histological diagnosis from prostate biopsy of PCa considered for radical prostatectomy as primary therapy, as a therapeutic choice shared with the doctor and in accordance with international guidelines. This treatment will follow normal clinical practice for this pathology and regular clinical and therapeutic procedure. Staging of these patients will be non-metastatic PCa at imaging (multiparametric magnetic resonance of the prostate).-Subgroup 2: Patients with initial histological diagnosis from prostate biopsy of advanced metastatic PCA (mHSPC) to be subjected to standard pharmacological treatments with androgen deprivation (ADT) and new androgen-targeted treatments (ARPI) or chemotherapy with taxanes, as a therapeutic choice shared with the doctor and in accordance with international guidelines. This treatment will follow normal clinical practice for this pathology and regular clinical and therapeutic procedure. Staging of these patients will be metastatic at imaging (PET CT scan or bone scan and CT scan).-Subgroup 3: Patients with initial diagnosis of BPH who have not undergone treatments. A healthy control population is not included but the BPH population will be used as a control. The clinical comparison will use male subjects of the same age (40–75 years) to determine the expression of a potential marker for prostatic neoplasia, involving the evaluation of differences within a population with benign prostatic pathology such as BPH and not healthy subjects (those without BPH) of mismatched age.

#### 6.4.1. Subgroup 1 and 2

Inclusion criteria: Male patients aged between 40 and 75 years, of any ethnicity, with an initial histological diagnosis of PCa from prostate biopsy. Non-metastatic versus metastatic clinical stage, intermediate or high-risk class according to d’Amico, indication as primary treatment for radical prostatectomy (Subgroup 1) or systemic therapy with androgen deprivation and ARPI or taxanes (Subgroup 2).

Exclusion criteria: Local or systemic therapies for PCa, other neoplasms in the active phase or undergoing treatment, ongoing oncological therapies (chemotherapies, target therapies, radiotherapies), hormonal or steroid therapies in progress or with drugs known to interfere with the evaluation foreseen in the study.

#### 6.4.2. Subgroup 3

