### 6.5. Methods

Under a regime of fasting from liquids and solids from midnight the previous evening, in the morning around 8.00 AM a blood sample will be taken from all patients. In Subgroup 1 and 3, the blood sample will be obtained only at baseline. In Subgroup 2, the blood sample will be obtained at baseline before the beginning of therapy and at 3-, 6-, 12-month intervals during systemic therapy. Sample storage will be performed at room temperature for 30 min, followed by centrifugation of the sample (3000× *g*; duration: 15 min) and subsequent separation to obtain a plasma sample. The plasma samples will be transported within 30 min to the chemistry laboratory in a suitable refrigerated container with ice at a temperature of 4 °C after centrifugation of the blood to remove the erythrocytes. As soon as they are delivered to the laboratory, the plasma samples appropriately labeled with the sample identification code will be stored at −80 °C until analysis.

For protein and metabolite corona experiments, in collaboration with the nanodelivery Lab of Sapienza of Rome, we developed a cross-reactive sensor array platform with cancer detection capacity made of three liposomal formulations with different surface charges, i.e., cationic 1,2-Dioleoyl-3-trimethylammonium propane (DOTAP), anionic 1,2-Dioleoyl-sn-glycerol-3-phosphoglycerol (DOPG), and a zwitterionic mixture made of dioleoylphosphatidylcholine (DOPC) and cholesterol [19]

For the proteomics–NP studies, proteins will be identified and quantified by nano-high-performance LC (nanoHPLC) coupled to MS/MS (nanoHPLC−MS/MS). The acquired raw MS/MS data files from Xcalibur software (version 2.2 SP1.48, Thermo Fisher Scientific, Washoe County, NV, USA) will be searched against the Swiss-Prot human database using the MaxQuant search engine with the automatic setting for tryptic peptide matching and label-free analysis. For each NP type, a list with all the identified proteins and their relative protein abundance (RPA, a quantitative estimation of their abundance within the protein corona) will be provided. The list of proteins will be utilized to discover new biomarkers associated with the PCa using sensor array technology [20].

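### The second primary endpoint is meant to personalise therapy in mHSPC, but one non-randomised treated cohort can show prognosis only, and prediction is not kept apart from on-treatment monitoring

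*Protocol article*

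**What the plan says.** **The aim.** The second primary endpoint (Section 6.3.2) is the "construction of a predictive model for the response to treatment of patients with an initial diagnosis of mHSPC for the personalization of therapies". Section 6.3.1 gives the same direction of travel, "leading to the development of personalized therapeutic strategies for patients". In the same sentence it names a second purpose, "to improve the precision and efficiency of monitoring treatment outcomes". The conclusions (Section 7) put forward, as a hypothesis, that corona systems could help tailor treatment options.

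**The cohort.** Section 6.2 speaks of "patients allocated in a 1:1:1 ratio of one of the three arms". Section 6.4 shows what these arms are: "Three different populations will be considered and compared", namely non-metastatic prostate cancer, mHSPC and BPH. Men with mHSPC (Subgroup 2) all receive androgen deprivation and "new androgen-targeted treatments (ARPI) or chemotherapy with taxanes, as a therapeutic choice shared with the doctor", under guidelines and normal practice.

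**The samples.** In Subgroup 2, "the blood sample will be obtained at baseline before the beginning of therapy and at 3-, 6-, 12-month intervals during systemic therapy" (Section 6.5). Section 6.2 adds: "A longitudinal analysis will also be applied to a 12-month interval observation".

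**The analysis.** Section 6.6 names PCA, OPLS-DA and PLS-DA. It describes no comparison of marker effects between regimens, and nothing in the article says which of the four samples enter the response model.

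**The concern.** A marker can be related to response in two ways. A prognostic marker separates men who do well from men who do badly whatever they are given. A treatment-predictive marker separates men who do better on one regimen from men who do better on another. Only the second kind helps to choose a therapy, and showing it requires comparing the marker's effect between treatments given to comparable men. Subgroup 2 has no randomised comparison and no untreated group.

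A second matter is timing. A sample taken on treatment may carry the effect of the drug or a response already under way. It can serve monitoring, but it does not exist when the first therapy is chosen.

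At stake is the reading of a primary result. A model that discriminates well would meet the endpoint as worded and could be taken as guidance for selecting treatment, which the data would not support.

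**Working it through.** The article gives no sample size, response rate or effect size for this endpoint, so there is no figure to reproduce. Every number below is an assumption or follows from one.

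**1. Is there a treatment contrast?** Set Section 6.2 beside Section 6.4. The three arms are three diagnoses, and a man's group follows from his disease. The 1:1:1 ratio therefore fixes group sizes and assigns no therapy. Within Subgroup 2 the regimen is a shared clinical choice, so the only contrast available is ARPI versus taxanes as chosen.

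**2. A strong marker with no value for choosing.** Assume response of 80% in marker-positive and 40% in marker-negative men, the same on both regimens.
- Odds ratio for response = (0.80/0.20) / (0.40/0.60) = 4.00/0.667 = 6.0.
- Difference between regimens: 80% − 80% = 0 in positives and 40% − 40% = 0 in negatives.

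**3. The same point for a continuous marker.** Let M be standard normal, with log-odds of response 0.4 + 0.8M under the regimen received (400,000 simulated men).
- Prognostic only (other regimen: −0.4 + 0.8M): AUC 0.70 under the regimen received, 0.70 under the other; interaction log-odds ratio 0.8 − 0.8 = 0.
- Predictive only (other regimen: −0.4): AUC 0.70 under the regimen received, 0.50 under the other; interaction log-odds ratio 0.8 − 0 = 0.8.

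Discrimination under the regimen received is identical, so it cannot tell the two apart.

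**4. Does comparing ARPI with taxane patients as treated solve this?** Assume an unmeasured severity factor U in half the men, a marker mean one unit higher when U = 1, log-odds of response 0.5 − 1.5U − 0.5M, and no regimen effect or marker-by-regimen interaction. Let the log-odds of receiving one of the regimens be −0.3 + s·U·(M − 0.5), and fit a logistic model with marker, regimen and their product.
- s = 0 (no selection): apparent interaction odds ratio 1.00.
- s = 1.0: 0.80.
- s = 1.5: 0.74.

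The true value is 1.00 throughout, so selection alone can produce an apparent interaction. The sizes depend on the inputs.

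**5. Regimen identity as a signal.** AUC from regimen alone = 0.5 + 0.5 × (share on the better-responding regimen among responders − share among non-responders).
- Response 80% and 60%, with 60% of men on the former. Responders: 0.48/(0.48 + 0.24) = 0.667. Non-responders: 0.12/(0.12 + 0.16) = 0.429. AUC = 0.62.
- Response 80% and 50%, split evenly. Responders: 0.40/0.65 = 0.615. Non-responders: 0.10/0.35 = 0.286. AUC = 0.66.

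An on-treatment profile that reveals the drug could reach these values without any information about the man. This is a reason to account for regimen.

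**6. Timing.** Of the four samples, only the one before therapy precedes the choice of regimen. If response is judged within the 12 months of Section 6.2, the 12-month sample falls at the end of that window and precedes no outcome in it.

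**7. Repeated samples, if pooled.** Assume 40 men, 4 samples each, 600 features unrelated to response, 7-fold validation and within-man correlation of 0.3 to 0.7. Splitting by sample gives a mean AUC of 0.97 to 1.00. Splitting by man gives 0.43 to 0.47, a little below 0.50 because scores are pooled over folds with unequal class balance; with balanced folds scored within fold it is 0.47 to 0.52. This shows why each man's samples should stay together. It does not describe the stated plan.

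**The case against.** The endpoint is the construction of a model, and personalisation is the purpose it should serve. Section 7 calls tailoring a hypothesis and asks for further clinical studies. That is fair: nowhere does the article promise to select therapy by corona profile, and a reader who infers such a promise goes beyond the text. But the purpose is written into a primary endpoint, and the design cannot serve it beyond generating a hypothesis.

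Subgroup 2 contains two kinds of regimen, so a marker-by-regimen contrast can be estimated. This also stands. It would be wrong to say that the data hold no information on the question; the estimate is confounded by indication, and none is described.

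A sample before therapy is planned, and Section 6.3.1 gives the later ones a monitoring purpose. Which samples enter which model may be settled in the full protocol or analysis plan. This stands to a large extent. A reader might infer that all four samples per man are pooled as independent rows and validated by sample, but the article states no validation scheme and announces a separate longitudinal analysis. What remains is that the article joins prediction and monitoring in one aim and does not say which samples serve which.

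**Conclusion.** The point holds in a limited form. As designed, the study can show whether the corona is associated with outcome among men treated for mHSPC. It cannot establish that the corona identifies which therapy a man should receive. This rests on Sections 6.2, 6.3.2 and 6.4 alone and on none of the assumed numbers. An analysis plan could not repair it, because the missing element is a comparison of treatments in comparable men.

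The separation of prediction from monitoring is secondary and is a matter of clarity, since the necessary baseline sample exists.

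The point concerns Subgroup 2 only, and the choice of regimen there is shared between patient and doctor. A reader might take the wording about arms and allocation as randomisation to treatment, but Section 6.4 excludes that. The AUCs and odds ratios above illustrate mechanisms under assumed inputs. In particular, the near-perfect AUC in step 7 is not a property of this trial.

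**What to change.** - Restate the second primary endpoint as a prognostic model of response in men starting systemic therapy for mHSPC.
- Name the pre-therapy corona as the predictor, with response assessed afterwards.
- Include regimen (ARPI or taxane) as a covariate or stratum. Label any marker-by-regimen interaction exploratory and state that it is open to confounding by indication.
- Describe personalisation in Sections 6.3.1 and 6.3.2 as hypothesis-generating.
- Analyse the 3-, 6- and 12-month samples separately as within-patient monitoring, for example with a mixed model or multilevel PLS-DA, and keep all samples from one man together in any validation.
- In Section 6.2, describe the arms as diagnostic groups recruited in equal numbers.

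The cost is wording in the protocol and analysis, with the same patients, samples and treatment. The price is a more modest claim. The change should be made before modelling begins.
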